### Eligibility criteria {10}

To be eligible for enrollment, participants must be ≥ 4 and < 13 years of age, have a confirmed diagnosis of non-CF BE (by high-resolution chest tomography (HRCT)), or if > 5 years since the last scan, under the regular care of a pediatric pulmonologist; experienced at least one acute pulmonary exacerbation in the past twelve months; and be medically able to participate in the exercise, have their parent provide informed consent, and not be planning to leave the study catchment area in the 12 months following enrollment. Participants will be excluded if they are unstable medically (as advised by the treating pulmonologist), have insufficient cooperation and/or cognitive understanding to perform tasks, have a recent musculoskeletal injury (e.g., muscle strain, sprains, fractures), have an underlying chronic illness other than BE (e.g., CF, neurological or cardiac disorders), are participating in a clinical trial of another investigational drug/devise or interventional therapy, and are unable to attend sessions or return for follow-up assessments.

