#### Sample size {14}

For the primary objective, the intervention effect is the difference in the percentage of children exacerbation free at 12-months follow-up. Based on the results of an RCT in which the percentage of children exacerbation free in the control group at 12 months was 18% [22], the percentage without an exacerbation over 12-months was estimated to be 20%. Based on the results of an exercise training RCT conducted on 55 adults with BE [12], we expect the therapeutic exercise program to double the percentage of children exacerbation free at 12 months follow-up from 20 to 40%. Assuming a 2-tailed alpha level of 0.05, a sample size of 79 per group (*N* = 158) will provide 80% power to detect the projected 20% group difference in the percentage of children exacerbation free at 12 months follow-up. To account for 10% attrition, a total of 174 participants will be recruited.

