### Assignment of interventions: allocation

#### Sequence generation {16a}

Participants will be randomly assigned to either the exercise group or the wait-list control group with a 1:1 allocation using a computer-generated randomization schedule, stratified by site using random permuted blocks sizes 2, 4, or 6.

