## Statistical methods

### Statistical methods for primary and secondary outcomes {20a}

The statistical analyses will follow standard principles for RCTs using two group comparisons including all participants on an intention-to-treat basis. For the primary objective, a binary regression model with a suitably chosen link function (e.g., logistic) will be used where the target variable is whether or not an exacerbation occurred over the 12-month study period for each subject. The main covariate of interest is the treatment group (exercise vs. wait-list control). Other covariates potentially influencing the target variable such as age and sex will be considered. Therefore, the statistically determined treatment effect will be appropriately adjusted for unbalanced data with respect to the other important covariates retained in the regression model. Between-group differences in secondary outcomes—aerobic fitness, habitual PA, perceived competence, HR-QoL (PedsQL), and lung function (FEV1)—will be tested immediately post-intervention, at 6 months follow-up, and at 12 months follow-up using linear regression with treatment group (exercise vs. wait-list control) as the main effect and baseline measures of the respective outcome, along with other potential confounders (e.g., age, sex), as covariates.

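### Site, the only randomisation stratum, is named in no model, and the primary model's covariates and link are left open, so the adjusted estimate and effect measure are not fixed

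*Protocol article*

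**What the plan says.** Protocol article, Sequence generation {16a}: allocation is 1:1 and "stratified by site using random permuted blocks sizes 2, 4, or 6". Site is the only stratum, and there are three sites.

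Protocol article, Statistical methods {20a}: for the primary outcome, "a binary regression model with a suitably chosen link function (e.g., logistic) will be used". Treatment group is the covariate of interest. For the rest, "Other covariates potentially influencing the target variable such as age and sex will be considered", and the treatment effect is then described as "appropriately adjusted for unbalanced data with respect to the other important covariates retained in the regression model". The secondary outcomes use linear regression with treatment group, the baseline value and other possible confounders, again with age and sex as examples. Site is named in neither place.

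Protocol article, Sample size {14}: "the intervention effect is the difference in the percentage of children exacerbation free at 12-months follow-up". The trial is therefore sized on an unadjusted difference in percentages, 20% against 40%.

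**The concern.** Three things are left loose in the one paragraph that defines the primary analysis.

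- **The stratum.** Allocation is balanced within site by design. A model without site ignores that balance when it estimates the standard error.
- **The covariates.** They are to be considered, adjusted for where unbalanced, and kept if important. No retention rule or final list is given. Read plainly, the set is settled once data are in.
- **The link.** The link sets the scale of the reported effect, and logistic is only an example. The sample size section defines the effect as a difference in percentages, which a logistic odds ratio does not report. An adjusted odds ratio also shifts with each prognostic covariate added, even when the difference in percentages stays the same.

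At stake is whether the primary estimate is the one that would have been written down beforehand, plus a small amount of power.

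**Working it through.** **1. The plan's own figure.** Inputs from Sample size {14}: two-sided alpha 0.05, 80% power, 20% v 40%. With unpooled variance:

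n = (1.96 + 0.8416)² × (0.2×0.8 + 0.4×0.6) / 0.2² = 7.849 × 0.40 / 0.04 = 78.49, so 79 per group.

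158 × 1.1 = 173.8, so 174. Both stated figures reproduce. A pooled-variance formula gives 82 per group, or 78.9% power at 79, which is a difference of convention.

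**2. One design effect, several effect measures.** For 20% v 40%:
- risk difference: 40 − 20 = 20 points
- odds ratio: (0.4/0.6)/(0.2/0.8) = 2.67
- risk ratio for being free of exacerbation: 0.4/0.2 = 2.0
- risk ratio for having one: 0.6/0.8 = 0.75

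Adding one covariate of assumed strength (log-odds 0.6, 0.8 or 1.0 per SD) moves the simulated median odds ratio from 2.7 to 2.9, 3.0 or 3.3 for the same 20% v 40%.

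**3. Does the link change the test?** Exact enumeration of Wald tests, 79 per arm, no covariates:

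| Link | Type I error | Power |
|---|---|---|
| Logit | 4.6% | 78.8% |
| Log (either coding) | 4.4–4.6% | 78.1–78.7% |
| Identity | 5.2% | 80.2% |

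The links disagree on significance in 0.7% of null trials and 2.1% of trials under the planned effect. The link matters for what is reported far more than for the P value.

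**4. Leaving site out.** The document gives no outcome rates by site, so these are assumptions: site shares w = 60/20/20%, site odds ratios from 1 to 2.7 and 0.135 relative to the largest site, and overall rates held at 20% and 40%. With p0 and p1 the site rates by arm:

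- true variance under site-balanced allocation: v = Σ w[p0(1−p0) + p1(1−p1)]/79
- variance the unadjusted analysis uses: u = 0.40/79
- power unadjusted: Φ((0.2 − 1.96√u)/√v); with site: Φ(0.2/√v − 1.96)
- type I error unadjusted: 2[1 − Φ(1.96√(0.16/Σ w p0(1−p0)))]

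Worked for the most extreme case, p0 = 0.192, 0.393, 0.031: Σ w p0(1−p0) = 0.6×0.155 + 0.2×0.239 + 0.2×0.030 = 0.147. Then 1.96 × √(0.16/0.147) = 2.05, and the type I error is 4.1%.

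| Control free of exacerbation, by site | Power unadjusted | Power with site | Type I error unadjusted |
|---|---|---|---|
| 20/20/20% | 80.2% | 80.2% | 5.0% |
| 22/22/12% | 80.4% | 80.8% | 4.9% |
| 21/31/6% | 81.0% | 82.7% | 4.5% |
| 19/39/3% | 81.7% | 84.8% | 4.1% |

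The loss from leaving site out is 0, 0.4, 1.7 and 3.1 points.

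**5. Choosing the covariates.** Logistic models, N = 158, blocks of 2, 4 or 6 within site, 3,000 runs per scenario (Monte Carlo error √(0.05×0.95/3000), about 0.4 points). Site effects are as in step 4. Assumed log-odds are 0, 0.3, 0.5, 0.8 per SD of age and 0, 0.3, 0.5, 0.5 for sex.

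| Scenario | Type I: unadjusted | Type I: age/sex kept at P<0.10 | Type I: smallest P of four age/sex models | Type I: site, age, sex fixed | Power: unadjusted | Power: site, age, sex fixed |
|---|---|---|---|---|---|---|
| None | 4.5% | 4.5% | 5.1% | 4.7% | 77.9% | 78.0% |
| Moderate | 4.9% | 5.2% | 5.8% | 5.2% | 78.7% | 80.6% |
| Strong | 4.3% | 4.9% | 6.1% | 5.5% | 79.9% | 83.4% |
| Very strong | 3.1% | 3.6% | 5.0% | 4.1% | 80.3% | 87.2% |

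Keeping covariates by their own P value does little. Picking the smallest treatment P adds about 0.6 to 1.9 points over the unadjusted model in the same scenario.

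**6. Room for the terms.** Children expected to be free of exacerbation: 79×0.2 + 79×0.4 = 15.8 + 31.6, about 47. Arm, two site terms, age and sex make five terms (47/5, about 9 each). A prior exacerbation count makes six (47/6, about 8 each).

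**The case against.** The strongest reply is that a covariate list, a link and a stratum term usually belong in the analysis plan, which is not shown, and that this is a condensed article. The covariate list is open, so it does not exclude site. Much of this stands: an unseen plan may settle every item before unblinding. What remains is that the article states a rule, tying adjustment to imbalance and retention, and that rule is worth replacing.

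Four stronger readings are tempting and are not supported.

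- **The link is chosen from the trial data.** The text leaves it open. It does not say when or on what basis it is chosen.
- **The trial is underpowered because site is left out.** The 80% is for an unadjusted comparison and reproduces. Leaving site out makes the test mildly conservative; the lost gain is zero if site is not prognostic.
- **Type I error is badly inflated.** A figure of 9 to 10% can be produced, but only by assuming four moderately prognostic covariates and searching all 16 subsets for the most favourable result. The article gives two example covariates and blinds the data analysts to allocation. Blinding limits such a search, although it does not fix the list or the scale.
- **A known strong predictor is already in hand and ignored.** Eligibility requires that a child "experienced at least one acute pulmonary exacerbation in the past twelve months", which every participant meets. Nothing says the number is recorded; baseline data mention only relevant medical history.

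Preferring a risk difference to an odds ratio is partly a matter of taste. Here it has a textual basis, because the sample size section defines the effect that way.

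**Conclusion.** The point holds as an inexpensive improvement. The document stratifies by site, names site in no model, and describes a covariate rule and link that do not determine one primary estimate or one effect measure. The effect on inference is modest: 0 to about 3 points of power and a type I error of about 4.1 to 5.0% when site is left out, 3.6 to 5.2% when age and sex are kept by P value, and about 5 to 6% under free choice among age and sex models. These ranges rest on assumed site shares, site differences and covariate strengths, since the document gives none. The main consequence is for the reported effect: the planned result could appear as 20 points, 2.67, 2.0 or 0.75. The sample size and its stated power stand.

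**What to change.** Before unblinding, in the protocol or the analysis plan:

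1. Include site in the primary model and in every secondary linear regression.
2. Adjust for age and sex as a set fixed in advance and kept whatever their observed balance or significance. Add the number of exacerbations in the 12 months before enrolment only if the sponsor confirms that it is recorded at baseline.
3. Delete the wording on retained covariates and on unbalanced data.
4. Name one link, logistic, and report the standardised (marginal) risk difference with 95% CI alongside the odds ratio, so that the result matches the difference the trial is sized on.
5. State beforehand how a very small site would be pooled, so that this does not become a new data-dependent choice.

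The cost is wording and a few model terms on about 47 expected exacerbation-free children. No change to the sample size is needed. The prior exacerbation count costs nothing extra only if it is already collected.

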**Methods:**

This multi-center, observer-blinded, parallel-group (1:1 allocation), randomized controlled trial (RCT) will be conducted at three sites. One hundred and seventy-four children ≥ 4 and < 13 years of age with BE will be randomized to a developmentally appropriate, play-based therapeutic exercise program (eight, 60-min weekly sessions, supplemented by a home-based program) or usual care. After completing the baseline assessments, the number of exacerbations and secondary outcomes will be assessed immediately post-intervention, after 6 months of follow-up, and after 12 months of follow-up. Monthly, parental contact and medical review will document acute respiratory exacerbations and parameters for cost-effectiveness outcomes.

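### Randomisation is stratified by site, but the covariate rule neither names nor fixes site in the primary or secondary models; if sites differ, a little power is forgone

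*Protocol article*

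**What the plan says.** All places are in the protocol article.

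- Sequence generation {16a}: allocation is 1:1, "stratified by site using random permuted blocks sizes 2, 4, or 6". The abstract states that the "randomized controlled trial (RCT) will be conducted at three sites".
- Statistical methods {20a}, primary outcome: "a binary regression model with a suitably chosen link function (e.g., logistic) will be used", with treatment group as the covariate of interest. On further terms: "Other covariates potentially influencing the target variable such as age and sex will be considered". The section then says the treatment effect will be adjusted for imbalance in whichever important covariates the model retains.
- Statistical methods {20a}, secondary outcomes: linear regression on treatment and the baseline value, "along with other potential confounders (e.g., age, sex), as covariates".
- Methods for additional analyses {20b} plans nothing further, and the missing-data section {20c} does not list the variables of the imputation model.

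Site is not named as a covariate in any of these analysis sections.

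**The concern.** Blocking within site makes the arms nearly equal in size at each hospital, which removes between-site variation from the treatment comparison. A model without site still counts that variation as error. Its standard error is then too large whenever sites differ in outcome, and the design's gain in precision goes unused.

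The stated rule makes omission likely. It gives three grounds for a covariate: possible influence on the outcome followed by retention, imbalance between arms, and potential confounding. Stratification prevents material imbalance and confounding by site, so two of the grounds point away from it. The remaining one leaves site to an unspecified retention step. The two covariates that are named were not stratified on, and the one factor that was is not named.

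At stake are some precision in the primary test and the secondary comparisons, and one avoidable choice about the primary model left open until the data are in.

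**Working it through.** **Inputs from the protocol article.** Three sites, 1:1 allocation stratified by site, exacerbation-free proportions of 20% (control) and 40% (exercise), two-sided alpha 0.05, 80% power, 79 per group, 10% attrition, total 174. The odds ratio is (0.40/0.60)/(0.20/0.80) = 2.67, log odds ratio 0.981.

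**Assumed, because the documents give no figures.** Site shares (60/20/20 or equal thirds) and site differences (logit offsets +d, 0, -d).

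**1. The planned size.** With unpooled variance, n = (0.16 + 0.24)(1.960 + 0.842)² / 0.20² = 78.5, rounded up to 79 per group, as stated. 158 × 1.1 = 173.8, which gives the stated 174. The calculation uses no site term, so 80% is the power of a comparison that ignores site.

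**2. Primary outcome, by simulation.** Model: logit(p) = a + site offset + b × treatment. The values a and b were solved so that the proportions averaged over sites stay at 20% and 40%. Arms were balanced within site, about 79 per arm, with 40,000 trials per scenario. Under the null both arms have the control rates. Logistic Wald tests were compared without and with site. Monte Carlo standard errors are √(0.05 × 0.95/40,000) = 0.1 points for type I error and √(0.8 × 0.2/40,000) = 0.2 points for power.

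| Shares | d | Control rates by site (%) | Type I error, without / with site (%) | Power, without / with site (%) | Log OR, marginal / site-conditional |
|---|---|---|---|---|---|
| 60/20/20 | 0 | 20.0, 20.0, 20.0 | 4.6 / 4.8 | 78.8 / 79.1 | 0.981 / 0.981 |
| 60/20/20 | 0.5 | 24.4, 16.3, 10.6 | 4.4 / 4.9 | 79.5 / 80.6 | 0.981 / 1.008 |
| 60/20/20 | 1 | 27.6, 12.3, 4.9 | 4.0 / 4.9 | 79.9 / 82.7 | 0.981 / 1.070 |
| Thirds | 0.5 | 28.2, 19.2, 12.6 | 4.2 / 4.8 | 78.3 / 79.8 | 0.981 / 1.014 |
| Thirds | 1 | 35.9, 17.1, 7.0 | 3.7 / 4.9 | 79.1 / 83.0 | 0.981 / 1.109 |

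The power gaps are 1.1, 2.8, 1.5 and 3.9 points. The log odds ratio is nearer zero by 1 - 0.981/1.008 = 2.7%, then 8.3%, 3.3% and 11.5%. At the extreme d = 1.5, type I error without site is 2.7-3.7%, power is 80-81% against 85-88%, and the log odds ratio gap is 14-22%. A separate simulation with 60/20/20 shares agreed: power 79.8% against 80.9% at d = 0.5, and 79.3% against 82.1% at d = 1.

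The type I error gap is not wholly due to site. The Wald test without site is already at 4.6% when sites do not differ, so about 0.2-0.3 points of each gap come from the test itself.

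**3. Secondary outcomes, closed form.** If site explains a share R² of the residual variance and is balanced by design, the statistic without site is about √(1 - R²) times the site-adjusted one. Type I error is then 2Φ(-1.960/√(1 - R²)). Where the adjusted test has 80% power, the test without site has Φ(2.802 - 1.960/√(1 - R²)).

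- R² = 1%: critical value 1.970, type I error 4.9%.
- R² = 5%: critical value 2.011, type I error 4.4%, power Φ(0.791) = 78.5%.
- R² = 10%: critical value 2.066, type I error 3.9%, power Φ(0.736) = 77%.

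**The case against.** **The lists are open.** They give examples, and nothing excludes site. A condensed article may leave the full covariate list to an analysis plan that is not shown. This stands as far as it goes: the text does not say that site will be omitted, and stratifying by site does not contradict naming age and sex as examples. But the article does more than stay silent. It states a rule for choosing covariates, and that rule gives no reason to keep site.

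**Site differences are assumed.** This also stands. The setting section describes services and staffing, and the background reports how prevalence varies between populations. Neither gives exacerbation-free rates among enrolled children, all of whom have bronchiectasis and at least one exacerbation in the past year. If sites do not differ, including site changes almost nothing.

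**Readings that go too far.** A reader might infer that the trial falls short of its 80% power. Fixing the within-site odds ratio at 2.67 and spreading the control rates to 30/15/5% in sites of 94, 32 and 32 children does give 73.6% without site and 77.1% with it. But those rates average to 21.9% and 40.7%, a difference of 18.8 points instead of 20. A plain two-proportion calculation on them, with no stratification, already gives 74.0%. Nearly all of the fall is the smaller assumed effect, and only the gap between the paired figures belongs to site.

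A reader might also call the smaller log odds ratio biased. It is the marginal odds ratio, which differs from the site-conditional one because odds ratios do not collapse over strata. The sample size section defines the effect as a difference in percentages, which omitting site does not bias, and the link is not yet fixed.

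**The error is in the safe direction.** True: a conservative test raises no false-positive risk.

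**Conclusion.** The point holds as a modest and inexpensive improvement. The trial randomises within site, but its analysis section does not commit to site in any model and applies a covariate rule that gives no reason to keep it.

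If site is left out and sites differ by ±0.5 to ±1 on the logit scale, the primary test runs at about 3.7-4.4% where the site-adjusted test runs at about 4.9%, and forgoes about 1-4 power points. The secondary models forgo about 1.5-3 points if site explains 5-10% of residual variance. All of this depends on assumed site shares and differences. The documents support neither a loss of the planned 80% nor a biased treatment effect. The validity of the comparison and the sample size are unaffected.

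**What to change.** In Statistical methods {20a}, state that site (three levels, two indicator terms) is a fixed effect in the primary binary model and in every secondary linear model, and that it stays in whatever happens to other covariates. In the missing-data section {20c}, include site in the imputation model so that imputation and analysis agree. If the logit link is kept, say that the odds ratio is conditional on site.

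This takes a few words in two sections and two degrees of freedom per model. No new data are needed, since site is already recorded for randomisation, and the sample size does not change. Settling it before outcome data are seen also removes one later choice about the primary model.

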### Interim analyses {21b}

Interim analyses are not planned.

### Methods for additional analyses {20b}

No other additional analyses are planned.

### Methods in analysis to handle protocol non-adherence and any statistical methods to handle missing data {20c}

Data will be analyzed using an intention-to-treat approach. Significant protocol non-adherence and drop-out are not anticipated, and any expected drop-outs are factored into the target sample size. Missing data will be imputed using multiple imputation procedures under the assumptions of missing at random (MAR) and multivariate normality. The imputation step will be implemented using the Markov chain Monte Carlo (MCMC) method in SAS PROC MI. PROC MIANALYZE will be used to combine the results into a single set of parameter estimates, standard errors, and test statistics [44].

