### Trial design {8}

The BREATH trial is designed as a randomized, controlled, multi-center, observer-blinded, parallel-group (1:1 allocation), superiority trial. Following informed consent/assent, enrolled children will complete baseline assessments (T1). Participants will then be randomized to either the therapeutic exercise program or wait-list control condition. The number of exacerbations and secondary outcomes will be assessed immediately post-intervention at 9 weeks (T2), after 6-months of follow-up (T3), and after 12 months of follow-up (T4).

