#### Primary outcome

Pulmonary exacerbation will be defined as treatment with antibiotics for any of the following: increased wet cough, dyspnea, increased sputum volume or color intensity, new chest examination or radiographic findings, deterioration in FEV1 percentage by more than 10%, or hemoptysis [22]. Wet cough must be present. Monthly, parental contact and medical review at each assessment time point will document acute respiratory exacerbations.

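### The multivariate-normal imputation rule makes no exception for the yes/no primary outcome, so the planned binary regression cannot use the imputed values without an unstated rounding step

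*Protocol article*

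**What the plan says.** In the Protocol article, Statistical methods for primary and secondary outcomes (item 20a), the primary analysis is a binary regression with a link such as logistic, and "the target variable is whether or not an exacerbation occurred over the 12-month study period for each subject". All participants are analysed by intention to treat.

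The section on non-adherence and missing data (item 20c) gives one rule: "Missing data will be imputed using multiple imputation procedures under the assumptions of missing at random (MAR) and multivariate normality". The method is MCMC in SAS PROC MI, with results combined by PROC MIANALYZE. The rule covers missing data in general. The section does not except the binary primary outcome, names no imputation method for categorical data and gives no rounding rule. Item 20b plans no additional analyses.

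On how events are captured, the Primary outcome section says: "Monthly, parental contact and medical review at each assessment time point will document acute respiratory exacerbations". Item 26b has parents consent to the use of a withdrawn child's data.

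**The concern.** The two method statements do not fit together. The analysis model needs a two-valued response. The imputation model treats that response as a continuous normal variable and returns values such as 0.37, 1.2 or -0.1. The analyst must then either leave the planned binary model or convert the values by a rule chosen later.

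This affects the trial's only primary test. A conversion rule chosen after the data are in is an avoidable analyst decision. The common choice, rounding at 0.5, does not preserve the proportion: it pulls both arms towards 50%, the control arm more, and so pulls the arms together. With no additional analyses planned, the article contains no check that would show the effect.

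**Working it through.** **Inputs (Sample size, item 14; Trial design, item 8).** The program is expected to "double the percentage of children exacerbation free at 12 months follow-up from 20 to 40" per cent, so the exacerbation risks are 80% (control) and 60% (exercise). Further: "Assuming a 2-tailed alpha level of 0.05, a sample size of 79 per group"; "will provide 80% power to detect the projected 20% group difference"; "parallel-group (1:1 allocation), superiority trial"; "To account for 10% attrition, a total of 174 participants will be recruited".

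**The plan's own figure.** The unpooled two-proportion formula gives n = (1.96 + 0.8416)² × (0.20×0.80 + 0.40×0.60) / 0.20² = 7.849 × 0.40 / 0.04 = 78.49, so 79 per group. Then 158 × 1.10 = 173.8, so 174. The stated sizes are reproduced, and the risks can be used as inputs. At 10% attrition about 17 of 174 children would leave.

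**Draws for a 0/1 variable, each arm with its own variance.** Draw from N(p, p(1−p)), where p is the exacerbation risk.

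- Control, p = 0.80, SD = √0.16 = 0.400. Above 1: P(Z > 0.50) = 30.9%. Below 0: P(Z < −2.00) = 2.3%. Outside 0 to 1: about 33%.
- Exercise, p = 0.60, SD = √0.24 = 0.490. Above 1: P(Z > 0.816) = 20.7%. Below 0: P(Z < −1.225) = 11.0%. Outside 0 to 1: about 32%.
- Rounding at 0.5: control P(Z > −0.75) = 77.3% instead of 80%; exercise P(Z > −0.204) = 58.1% instead of 60%.

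**The same with one common variance.** A normal model with arm as a predictor has a single residual variance, here (0.16 + 0.24)/2 = 0.20, SD 0.447. About 36% (control) and 28% (exercise) of draws fall outside 0 to 1. Rounding makes the exacerbation-free share 25.1% instead of 20% and 41.2% instead of 40%.

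**Effect on the trial estimate.** Only imputed children are affected.

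- Own variances: the difference among imputed children is 77.3 − 58.1 = 19.2 points instead of 20. At 10% imputed, the loss is 0.10 × 0.8 = 0.08 points.
- Common variance: 41.2 − 25.1 = 16.1 points instead of 20. The loss is 0.10 × 3.9 = 0.4 points at 10% imputed and 0.8 points at 20%.

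**Simulation.** N = 174, 1,500 trials, 20 imputations, risk-difference scale with Rubin's rules. Assumptions that are not in the article: constant exacerbation hazard, uniform drop-out times, arm as the only predictor, and, for the two normal methods, every drop-out coded as missing. The replacement keeps documented exacerbations as events and draws the remaining months of event-free leavers as a 0/1 outcome.

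| Drop-out | Method | Mean difference | Power |
|---|---|---|---|
| 10% | normal, unrounded | 0.200 | 79.1% |
| 10% | normal, rounded | 0.196 | 78.0% |
| 10% | replacement | 0.200 | 81.4% |
| 20% | normal, unrounded | 0.200 | 74.3% |
| 20% | normal, rounded | 0.192 | 70.8% |
| 20% | replacement | 0.200 | 78.1% |

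Rejection under the null is about 4 to 6% for every method. Each power has a Monte Carlo standard error of about 1 point (√(0.8 × 0.2 / 1,500) = 0.010). The replacement changes two things at once, so its gain in power cannot be credited to the binary method alone. The step from unrounded to rounded isolates the rounding: about 1 point of power at 10% drop-out and 3.5 points at 20%.

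**The case against.** The strongest reply is that the article is condensed and that a rounding step, which would let the binary model run, may stand in the full protocol or analysis plan. The effect is also small. With about a tenth of the outcomes imputed, rounding costs at most a few tenths of a point of the planned 20, and the type I error holds.

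The point on size stands. The point on condensation stands only in part. The article does not leave the imputation model open. It names one, and that model does not suit the article's own primary outcome. That is a stated choice to correct, whatever detail lies elsewhere.

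A reader might go further and infer that exacerbations documented before drop-out will be overwritten by imputed values. The article does not support this. Item 20c imputes missing data only. Under the item 20a definition, a child with one documented exacerbation already has a known outcome. Events are recorded monthly, and a withdrawn child's data may be used. No section codes such a child as missing. Equally, none states that the child is kept as an event, so one sentence would close the risk.

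**Conclusion.** The point holds as a mismatch of methods: a multivariate-normal imputation rule without exception, next to a yes/no primary outcome in a binary regression. About a third of draws would be impossible as probabilities, practically none would be 0 or 1, and the primary model needs a conversion step that the article does not state.

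The numerical consequence is small at the planned 10% attrition: 0.08 to 0.4 points off a 20-point difference with rounding at 0.5, depending on the variance used, and about 1 point of power from the rounding itself. It grows with drop-out. These sizes rest on the planned risks, and the power figures also on the simulation assumptions listed above.

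A reader might infer a materially biased primary result or lost events. Neither follows from the text. Left unrounded on the risk-difference scale, the normal method showed negligible bias. The severity is moderate: the reason to act is that a decision within the primary analysis is left open, and closing it costs little.

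**What to change.** 1. In item 20c, restrict the multivariate-normal MCMC method to the continuous secondary outcomes.
2. For the primary outcome, name an imputation method for binary data, for example PROC MI with FCS LOGISTIC, or MONOTONE LOGISTIC if the missing pattern is monotone. Include arm and a small set of baseline covariates. A large model fitted by arm and by interval is not needed and risks sparse cells: about 16 of 79 control children (0.20 × 79) are expected to be exacerbation free at 12 months.
3. As a clarification, state that one documented qualifying exacerbation settles the outcome as yes whatever the later follow-up, so that only children event-free at drop-out are imputed. The imputation should then reflect the time already spent event-free. Under a constant hazard (assumption), a control child event-free at 6 months has probability √0.20 = 0.447 of remaining so to 12 months, against 0.20 for a control child at the start. One term for event-free follow-up time would serve.

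The cost is a few sentences in the protocol or analysis plan and a few lines of SAS code. No new data are needed. The wording should be settled before unblinding.
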